#### Parent knowledge and self-efficacy

Change in parent knowledge, self-efficacy, and outcome expectations regarding child nutrition and obesity prevention is assessed using questionnaires specific to POPS, and knowledge and self-efficacy regarding parenting and child behavior is assessed with questionnaires developed by IYS.

### Secondary outcome measures, covariates, and demographics

Additional constructs that may relate to obesity and/or self-regulation (e.g., maternal depression; child temperament) are also assessed. Parents complete the Caregivers’ Feeding Styles Questionnaire, [77] Dutch Eating Behavior Questionnaire, [78] USDA Household Food Security Scale, [79] Center for Epidemiologic Studies Depression Scale, [80] Child Behavior Questionnaire-Short Form, [81] The Parenting Scale, [82] and the Alabama Parenting Questionnaire [83]. Parents and teachers both complete the Eyberg Child Behavior Inventory (Student Behavior Inventory version for teachers) [84]and the Social Competence and Behavior Evaluation [85]. Following ATDG, children participate in Gift Delay- Wait, Bow and Wrap Tasks [86] to assess non-food-related self-regulation, and in brief interviews to assess their emotion knowledge [87], a focus of IYS. Because an element of each intervention is classroom-based and results may reflect classroom-level processes, independent observers also assess the emotional climate of the classroom and teachers’ support of children’s self-regulation (fall and spring) via the Caregiver Interaction Scale [88] and the Supports for Social-Emotional Growth Assessment [89]. Teachers also report their use of IYS classroom management strategies using the Teacher Strategies Questionnaire [55]. Finally, parents provide demographic data, including child sex, race, ethnicity, maternal education, family income-to-needs ratio, family structure, and child’s birth weight and gestational age.

### Process evaluation measures

Process data is gathered to assess intervention implementation and feasibility. Data include parent attendance at sessions, parent satisfaction with program elements, and reasons for not attending sessions or withdrawing from the study (via exit interviews). Child school attendance and participation in the lessons is also recorded.

In addition to implementation fidelity observations (described above), HS Staff and Extension Educators complete questionnaires regarding intervention buy-in (e.g., perceived need for and interest in the intervention, time devoted to implementation), and are interviewed on a quarterly basis regarding intervention strengths/weaknesses, implementation issues, and challenges of retention.

### Sample size, power calculations, and data analysis

#### Sample size and power calculations

Enrolling 200 participants per arm, assuming attrition of 25%, will achieve a final sample size of 150 participants per arm. This sample size of 150 per arm will enable detection of small to moderate effect sizes of f = .16 (between groups vs. within group variation), with a power of 80%, α = .05 and assuming and intraclass correlation *r* = .05. This sample size also provides 80% power with *r* = .20, α = .05 to detect an effect size of f = .185.

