### Study aims and hypotheses

The primary aim of this study is to examine the effectiveness and feasibility of the two obesity prevention interventions described above: 1) POPS and 2) POPS + IYS, as delivered by community-based nutrition educators and HS staff to low-income preschoolers and their parents. Hypotheses are that across an academic year, compared to Usual HS Exposure: (1) POPS will result in improved obesity-related health behaviors and adiposity indices; (2) POPS + IYS will result in the greatest improvement in obesity-related health behaviors and adiposity indices, and this greater effect will be mediated in part by increased child self-regulatory capacity. A process evaluation to assess the feasibility, fidelity, parental engagement, and educational effectiveness of the POPS and POPS + IYS interventions will also be conducted. This project was funded by the USDA National Institute of Food and Agriculture (NIFA) Agriculture and Food Research Initiative (AFRI) Competitive Grants Program, Childhood Obesity Prevention Challenge Area.

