#### Analysis plan

The primary objective is to determine whether POPS + IYS is more effective, compared to POPS alone or Usual HS Exposure, in reducing adiposity measures (BMI z-score, skinfolds thickness). Additional focal outcomes are dietary intake, TV viewing, ATDG, emotional eating, and food-related tantrums. Baseline comparability of the 3 groups will be assessed. To account for clustering of children within a classroom, Proc Mixed in SAS with a random intercept for classroom will be used to analyze continuous outcomes, and General Estimating Equations (GEE) techniques [90] will be used to compare the prevalence of obesity and overweight across the 3 groups. Analyses will be conducted both with and without adjustment for baseline characteristics such as age, sex, race, and baseline BMI or BMI z-score. All models will incorporate covariates that are related to the outcomes to reduce residual variance and thus help reduce Type II error. Significance will be assessed using a two-sided test at α = 0.05.

Analyses will be based on the intention to treat principle where all randomized participants, including dropouts, are included in the analysis based on their randomized intervention group [90]. Given that a substantial portion of participants will likely have only partial adherence to the intervention (e.g., only attend some parent sessions), dose–response analyses will also be performed where dose corresponds to number of sessions attended.

As outlined in the conceptual model (Figure 1), analyses will be conducted to test whether the effect of POPS + IYS on obesity-related health behaviors and adiposity indices is mediated by self-regulation (using parent-reported, teacher-reported, and direct child assessment measures). As a secondary analysis, models will also be examined separately for boys and girls, white and non-white children, and children who are overweight or obese versus non-overweight at baseline.

Finally, process data on recruitment, retention, participant engagement in the intervention, participant and educator satisfaction, and implementation fidelity will be analyzed using descriptive and qualitative approaches, to inform continued collaborations with HS and allow more effective dissemination of findings.

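### The 80% power is stated for a three-group omnibus f, but the primary objective is pairwise; without covariate adjustment, f = .16 gives POPS + IYS versus POPS less than 80% power however the three ordered means are spaced

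*Protocol article*

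**What the plan says.** The section on sample size and power gives the numbers analysed: "Enrolling 200 participants per arm, assuming attrition of 25%, will achieve a final sample size of 150 participants per arm". It states the detectable effect as "effect sizes of f = .16 (between groups vs. within group variation), with a power of 80" per cent, α = .05, "assuming and intraclass correlation *r* = .05". A second scenario follows: "This sample size also provides 80% power with *r* = .20, α = .05 to detect an effect size of f = .185". No pairwise difference, pattern of means or contrast-level power is given.

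The analysis plan puts the objective in terms of contrasts: "The primary objective is to determine whether POPS + IYS is more effective, compared to POPS alone or Usual HS Exposure". Testing is two-sided: "Significance will be assessed using a two-sided test at α = 0.05". The aims section hypothesises that POPS improves on Usual HS and that "POPS + IYS will result in the greatest improvement in obesity-related health behaviors and adiposity indices". This fixes the order Usual HS, POPS, POPS + IYS, but not the distances between them.

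The study design section gives 75 classrooms randomised to three arms of 200 children.

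**The concern.** Cohen's f is the standard deviation of the group means divided by the within-group standard deviation. A significant three-group F test shows that the means are not all equal. It does not show that POPS + IYS is better than POPS, or which arms differ. The article's only power claim therefore concerns a different test from the one its primary objective needs.

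The contrast most affected is POPS + IYS versus POPS. It carries the trial's novel question, whether self-regulation training adds to obesity education. A reader who sees 80% power will naturally take it to cover that contrast. If POPS works at all, as the first hypothesis says, part of the spread behind f = .16 lies between Usual HS and POPS, and less is left between POPS and POPS + IYS.

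**Working it through.** **Inputs from the article.** 150 analysed per arm (450 in total); ICC .05 with f = .16; ICC .20 with f = .185; two-sided α = .05; 75 classrooms; three arms.

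**Derived.** An equal split gives 25 classrooms per arm, so m = 150/25 = 6 completers per classroom.

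**Assumed.** The spacing of the means and the fall-spring correlation r are not given, so ranges are shown.

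**1. The stated figure.** The design effect is 1 + (m − 1) × ICC = 1 + 5 × .05 = 1.25, so the effective total is 450/1.25 = 360. For a three-group F test with 2 and 357 degrees of freedom and noncentrality 360 × f², 80% power needs f = 0.164, which rounds to the stated .16. At exactly f = .16 the power is 77.7%. Reading f as a two-group effect (d = 2f = 0.32) gives 69.8%, a worse fit. The figure is best read as an omnibus effect.

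**2. From f to pairwise differences.** Put Usual HS at 0, POPS at λD and POPS + IYS at D in within-group SD units, with λ between 0 and 1. The variance of the three means is (2/9) × D² × (1 − λ + λ²), so

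D = f / √[(2/9)(1 − λ + λ²)].

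POPS + IYS versus POPS is then d = (1 − λ)D.

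**3. Pairwise power, unadjusted.** Effective n per arm is 150/1.25 = 120, so SE = √(2/120) = 0.129. Power is Φ(d/SE − 1.96). With f = .16:

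| λ (position of POPS) | d, POPS + IYS vs POPS | Power | d, POPS + IYS vs Usual HS | Power |
|---|---|---|---|---|
| 0 (equals Usual HS) | 0.339 | 74.8% | 0.339 | 74.8% |
| 0.25 | 0.282 | 59.0% | 0.377 | 83.1% |
| 0.5 (equal spacing) | 0.196 | 32.9% | 0.392 | 85.9% |
| 0.75 | 0.094 | 10.9% | 0.377 | 83.1% |
| 1 (equals POPS + IYS) | 0 | 5% (alpha level) | 0.339 | 74.8% |

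For example, at λ = 0.5, D = .16/√(1/6) = 0.392 and d = 0.196, so d/SE = 1.518 and Φ(1.518 − 1.96) = 32.9%.

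**4. Is the ceiling a rounding effect?** No. With the unrounded f = 0.1643, the largest d is 0.1643/√(2/9) = 0.3485, and Φ(0.3485/0.1291 − 1.96) = 77%. With m = 4 instead of 6, the ceiling at f = .16 is 78.3%.

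**5. Pairwise difference detectable with 80% power, unadjusted.** d = 2.80 × √(2/n):
- ICC .05, n = 120: d = 0.36 (0.362), above the largest gap that f = .16 allows under the ordering (0.339).
- ICC .20: design effect 1 + 5 × .20 = 2, n = 75, d = 0.46 (0.457).

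**6. With adjustment for the fall value.** Multiply d by √(1 − r²), treating the ICC as unchanged:

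| Assumed r | ICC .05 | ICC .20 |
|---|---|---|
| .5 | 0.31 | 0.40 |
| .8 | 0.22 | 0.27 |
| .9 | 0.16 | 0.20 |

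If f = .16 is on the raw-SD scale, power for POPS + IYS versus POPS at equal spacing (d = 0.196, ICC .05) becomes about 42% at r = .5, 72% at r = .8 and 94% at r = .9.

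**The case against.** **The label is open.** The article describes its f as between-group against within-group variation and never says that the 80% applies to POPS + IYS versus POPS. An omnibus f is a common convention for three arms, and contrast-level power may sit in a fuller document. This stands as far as it goes: the sentence is not false. But the article prints one power claim beside a pairwise objective, and that claim does not answer the objective.

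**One third is not the power of the trial.** A reader might infer that the hypothesised ordering itself implies about 33% power. The documents do not support that. They give an order and no spacing, and 33% needs equal spacing. Orderings consistent with the text give anything from the alpha level to about 75%.

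**Adjustment is planned.** The analysis plan runs models with and without baseline characteristics, including baseline BMI or BMI z-score, and brings in outcome-related covariates to reduce residual variance. With a high fall-spring correlation the power could be far above the unadjusted figures. Even at r = .5 the ceiling passes 80%: 0.339/(0.129 × 0.866) = 3.03, and Φ(3.03 − 1.96) = 86%. This stands, and it limits the shortfall at every spacing to the unadjusted case. The article gives no r and claims no such gain in its power section, so neither figure is established.

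**The ICC .20 scenario.** Applying f = .185 at 6 per classroom would show a larger shortfall, but that f does not reproduce there (omnibus power 69.4%; 79.5% at m = 4). Part of that gap is a separate cluster-size matter, so the power argument here rests on ICC .05.

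**Misuse of a null result.** A reader might also infer that the trial intends to conclude no added benefit from a non-significant contrast. No section plans this.

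**Conclusion.** The concern holds in this form: the article's 80% power belongs to an omnibus three-group effect, while its primary objective is two pairwise contrasts. At f = .16, POPS + IYS versus POPS has between 5% and 75% power depending on where POPS lies, with 33% at assumed equal spacing, and never 80%. The 75% end requires POPS to equal Usual HS, contrary to the first hypothesis. The other primary contrast, POPS + IYS versus Usual HS, is much better placed at about 75% to 86%.

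These figures assume 150 analysed per arm, 6 completers per classroom, ICC .05, two-sided α = .05 for each contrast and no covariate adjustment. They show that the stated power does not cover the key contrast on the stated terms. They do not show that the trial is underpowered under its adjusted analysis, because that depends on a correlation the article does not give.

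**What to change.** In the section on sample size and power, replace or supplement the omnibus f with the pairwise difference detectable with 80% power for each primary contrast:

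- unadjusted, 6 per classroom: d = 0.36 at ICC .05 and d = 0.46 at ICC .20;
- baseline-adjusted, with the assumed fall-spring correlation stated: for ICC .05, for example, d = 0.31 at r = .5, 0.22 at r = .8 and 0.16 at r = .9.

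Add one sentence saying that the 80% figure does not apply to POPS + IYS versus POPS at f = .16 without adjustment.

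The cost is a few lines of text and a less favourable stated figure. Enrolment, arms and analysis models do not change.

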## Methods/design

### Study design

The Growing Healthy study is a randomized controlled trial (RCT). Classrooms (*n* = 75) are randomized through an automated system to one of 3 study arms (200 children per arm): (1) POPS; (2) POPS + IYS; or (3) Usual HS Exposure. Each HS program hosts all 3 study arms, and all children in an individual classroom participate in only one arm. Only one classroom participates per physical school site to prevent cross-contamination across study arms and ensure that participants are blind to group assignments. Families are assigned to study arm as a function of their classroom assignment. Every effort is made to match intervention and comparison classrooms on demographic characteristics in order to minimize differences not due to the intervention (e.g., % minority race/ethnicity, teacher education).

Data are collected pre-intervention (in the fall) and post-intervention (in the spring). Interventions occur between October and April of the academic year. Process implementation data are collected throughout the study. Children are enrolled in each of 4 academic years, with 50 children enrolled into each of the 3 study arms per year. Data collectors are separate from the interventionists, and blinded to the study arm to which participants in a classroom are assigned.

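### With 75 classrooms and an intraclass correlation of .20, power for f = .185 is about 69%, not the stated 80%; the detectable effect is about f = .21.

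*Protocol article*

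**What the plan says.** The section on sample size and power calculations of the protocol article plans 200 children per arm, allows for 25% attrition, and so counts on 150 analysed per arm. It makes two power statements for that sample:

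- At an ICC of .05 ("assuming and intraclass correlation *r* = .05"), the sample "will enable detection of small to moderate effect sizes of f = .16" with 80% power.
- At a higher ICC, "This sample size also provides 80% power with *r* = .20", with "α = .05 to detect an effect size of f = .185".

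The section gives no number of children per classroom. The Study design section supplies what is needed to work it out: "Classrooms (*n* = 75) are randomized through an automated system" to three arms of 200 children each. The analysis plan confirms that clustering is handled at classroom level, by a random intercept for classroom in the mixed model.

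**The concern.** With sample size, α and power held fixed, the detectable effect grows with the square root of the design effect. Raising the ICC from .05 to .20 with 6 children per classroom should therefore raise the detectable f by a factor of √(2.0/1.25) = 1.265. The two printed values differ by a factor of only .185/.16 = 1.156. Even if rounding is pushed as far as it will go (.1855/.155), the factor is 1.197. The two statements cannot both describe a design with 6 analysed children per classroom.

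The ICC .20 sentence is the plan's only assurance that the trial still works if classrooms differ strongly. If that assurance is too favourable, a null result under strong clustering could be read as ruling out effects that the trial had a substantial chance of missing.

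**Working it through.** **Inputs**

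| Quantity | Value | Source |
|---|---|---|
| Arms | 3 | Study design |
| Classrooms | 75 (25 per arm if equal) | Study design |
| Children enrolled | 200 per arm, 600 in all | Study design; sample size section |
| Attrition | 25% | Sample size section |
| Children analysed | 150 per arm, 450 in all | Sample size section |
| Analysed per classroom, m | 450/75 = 6 | Derived |
| α | .05 | Sample size section; analysis plan |
| ICC | .05 and .20 | Sample size section |

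**Formulas**

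- Design effect: DE = 1 + (m − 1) × ICC
- Effective sample size: N_eff = 450/DE
- Power: the probability that a noncentral F with 2 numerator degrees of freedom (df) and noncentrality λ = f² × N_eff exceeds the central F critical value at α = .05. The denominator df is N_eff − 3, or 75 − 3 = 72 if counted at classroom level.

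**The plan's first figure (ICC .05, f = .16)**

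- DE = 1 + 5 × .05 = 1.25 and N_eff = 450/1.25 = 360.
- λ = .16² × 360 = 9.22.
- Power is 77.7% (76.3% with 72 df).
- The detectable f at 80% power is .164 (.167 with 72 df).

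The value .164 rounds to the stated .16, so this figure is reproduced to within rounding on the simpler df.

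**The plan's second figure (ICC .20, f = .185)**

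- DE = 1 + 5 × .20 = 2.0 and N_eff = 450/2.0 = 225.
- λ = .185² × 225 = 7.70.
- Power is 69.4% (68.0% with 72 df; 69.7% with 447 df).
- The detectable f at 80% power is .208 (.211 with 72 df).

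This figure is not reproduced. A simulation of classroom means (25 per arm, 6 children each, 40,000 runs) gave 68% for two patterns of arm means: equally spaced, and one arm differing from the other two. That matches the 72-df result.

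**What design would give the printed figures?**

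- For f = .185 at ICC .20, 80% power needs N_eff = 284.5. That is DE = 450/284.5 = 1.58, m = 1 + .58/.20 = 3.9, or about 115 classrooms.
- For f = .16 at ICC .05, it needs N_eff = 379.4. That is DE = 1.186, m = 4.7, or about 95 classrooms.

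**Other readings tried**

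| Reading | ICC .05: power at f = .16; detectable f | ICC .20: power at f = .185; detectable f |
|---|---|---|
| 450 analysed, 6 per classroom (the design) | 77.7%; .164 | 69.4%; .208 |
| 450 analysed, 5 per classroom | 79.5%; .161 | 74.3%; .1975 |
| 450 analysed, 4 per classroom | 81.3%; .1575 | 79.5%; .186 |
| 450 analysed, 2 per classroom | 84.9%; .1505 | 90.2%; .161 |
| 600 analysed, 8 per classroom, no attrition | 86.2%; .148 | 74.3%; .1975 |

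Only 4 per classroom recovers both printed effects. That implies 450/4 ≈ 112 classrooms, against the 75 stated. Two changes of test, α = .10 and a comparison of only the two most extreme arms, reach about 79% to 80% at ICC .20. Both give about 86% for f = .16 at ICC .05, so neither reproduces the pair.

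**The case against.** Three points can be made for the plan.

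1. **The cluster size of 6 is inferred.** The article does not say whether the 75 classrooms are distinct across the four enrolment years. If some classrooms returned with new cohorts, there would be more than 75 classroom-years and fewer than 6 analysed children in each, and about 4 would fit both figures. This cannot be excluded from the text, but nothing in the text states it. The Study design section ties the 75 classrooms to the full 200 children per arm, and the analysis plan puts the random intercept on classroom, not classroom-year.

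2. **Covariates may recover the power.** The analysis plan adjusts for variables related to the outcome, including baseline BMI or BMI z-score. Covariates explaining about 21% to 23% of the variance at both levels (a correlation of about .46 to .48) would restore 80% power for f = .185. The article gives no such correlation, so this is an assumption, though not a demanding one for BMI z-score measured in fall and spring. This point stands for adjusted analyses of adiposity: their real power may well be better than 69%. It does not rescue the printed statement, because the power section invokes no covariate gain. The same gain would also lift power for f = .16 at ICC .05 to about 87%, contradicting the 80% stated there. Unadjusted analyses are planned as well.

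3. **The consequence is limited.** The disputed number belongs to the second, more pessimistic scenario. Sample size, randomisation and analysis model do not depend on it. That is true, and it is why the remedy is only a correction of the text.

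**Conclusion.** The ICC .20 power statement is wrong for the design described. Power for f = .185 is 68% to 70%, 10 to 12 percentage points below the stated 80%. The chance of missing an effect of that size is about 31%, not 20%. The effect detectable with 80% power is f = .208 to .211. The ICC .05 figure is only marginally optimistic and is not in itself an error.

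The conclusion assumes that 75 is the total number of classrooms over all years, that they are split 25 per arm with equal numbers analysed in each, that the test is the three-arm comparison at α = .05, and that no covariate gain is counted. Unequal classroom sizes would lower power further. A real covariate gain would raise it, but would have to be stated and applied to both scenarios. The likely source of the discrepancy is a calculation based on about 4 children per classroom, though the article does not show this.

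**What to change.** Restate the ICC .20 sentence for the actual design: 75 classrooms, 6 analysed children in each, and 80% power for f = .208 (about .211 with 72 classroom-level df). Give the cluster size next to it so that the figure can be checked. For consistency, the ICC .05 figure can be given on the same basis as .164 (about .167 with 72 df).

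If the calculation was meant for a different number of classrooms or classroom-years, say so and reconcile it with the 75 in the Study design section. If a covariate gain was meant, state the assumed variance explained and recompute both scenarios with it.

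The cost is wording only. The stated detectable effect becomes less favourable, and no children or classrooms are added. For comparison, actually reaching 80% power for f = .185 at ICC .20 with 6 analysed per classroom would take about 99 classrooms (33 per arm).
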